## Abstract

**Background:**

Burn injuries severe enough to result in emergency department visits are a large burden for US children. Treatment for these injuries often involves daily dressing changes at home, which can be very painful and anxiety-inducing. This trial aims to evaluate the efficacy of a virtual reality therapeutic for pain and anxiety alleviation during repeated at-home burn dressing changes among pediatric patients.

**Methods:**

Two hundred children with burn injuries requiring daily dressing changes will be recruited from two American Burn Association-verified burn centers in the USA for this randomized, controlled, two-arm clinical trial with a 1:1 allocation ratio. During each dressing change at home, the intervention group will play the Virtual Reality Pain Alleviation Therapeutic (VR-PAT) game and answer questions about their pain, anxiety state, pain medication usage, simulator sickness symptoms, and experience playing the game. The control group will perform their dressing as usual without the VR-PAT and answer questions about their pain, anxiety state, and pain medication usage. The primary outcome is the difference in self-reported pain and anxiety between the two groups over their week of dressing changes.

**Discussion:**

The transition of burn injury treatment from the medical center to the home can increase anxiety for children and their parents. Virtual reality is a promising digital technology that can improve wound care for these children. Findings from this trial will provide data on the efficacy of the VR-PAT for reducing self-reported pain and anxiety during daily home dressing changes for pediatric burn care. The results from this trial will serve as evidence for a large-scale implementation study.

**Trial registration:**

ClinicalTrials.gov NCT05673551. Registered on December 21, 2022.

## Administrative information

Note: the numbers in curly brackets in this protocol refer to SPIRIT checklist item numbers. The order of the items has been modified to group similar items (see http://www.equator-network.org/reporting-guidelines/spirit-2013-statement-defining-standard-protocol-items-for-clinical-trials/).

## Introduction

### Background and rationale {6a}

According to the Centers for Disease Control and Prevention, there were about 122.9 per 100,000 US emergency department (ED) visits for nonfatal burn injuries among children (0–18 years) in 2023 [1]. Over half of the pediatric burn injuries seen in US EDs are severe enough to merit referral to a burn center according to the USA and international guidelines [2, 3]. After discharge from burn care facilities, repeated burn dressing changes are often needed at home for 2–3 weeks. Pediatric patients have identified dressing changes as very painful, with opioid and anxiety medications often being prescribed [4, 5]. Furthermore, the pain experienced during burn dressing changes may cause distress to caregivers [6]. A painful experience can also serve as a stressor that significantly impacts patients’ post-injury health outcomes [7, 8]. The medical community in the USA is working to find the right balance between the risk of undertreating pain and causing unneeded suffering [4, 5] and the risk of over (or inappropriate) prescription of opioids [9]. Therefore, there is a pressing need to seek non-pharmacological interventions for effective pain management in pediatric burn wound care.

Pediatric clinicians widely utilize non-pharmacological pain management as a safe and affordable solution for procedural acute pain management [10, 11]. According to the Cognitive-Affective Model of Pain [12], pain perception demands cognitive attention. Thus, effective non-pharmacological pain management requires the interruption of the cognitive route from the origin to pain perception, redirecting a child’s attention resources away from the painful procedure. Virtual reality (VR) has been demonstrated to effectively decrease pain and distress in a variety of settings, among diverse populations [13, 14], and targeting a wide range of pain conditions (i.e., acute, procedural, and chronic) [15]. Recent meta-analyses and reviews of published studies in the past three decades have provided evidence that VR can effectively help patients reduce pain and anxiety across many settings [14–18]. However, prior studies have not investigated the feasibility and barriers of VR games for pain management during at-home burn dressing changes. Nearly all existing studies used computer-based VR equipment that is technologically and financially inaccessible to many patient families for everyday use in the home.

Our previous clinical studies have provided strong evidence about the efficacy of smartphone-based VR Pain Alleviation Therapeutics (VR-PAT) for significant pain reduction during burn dressing changes. In our randomized controlled trial (RCT) in the outpatient burn clinic, patients were randomly assigned to an active VR-PAT, passive VR-PAT, or standard care group [19]. Active VR-PAT significantly reduced observed and self-reported pain during burn dressing changes, while patients and caregivers reported satisfaction with the VR-PAT. In another pilot study, pediatric patients were randomly assigned to VR-PAT or control to examine the feasibility of VR-PAT as a pain alleviation tool during at-home dressing changes [20]. Children found the VR-PAT to be a helpful distraction during home dressing changes and reported it to be easy to implement. Children playing the VR-PAT reported consistent happiness and fun as the week went on and increased realism and engagement, indicating that repeated use does not diminish its efficacy.

In this proposed study, we will evaluate the effectiveness of a hands-free, portable, affordable, and actively engaging VR-PAT for pain and anxiety alleviation during repeated at-home burn dressing changes.

### Objectives {7}

The objective of this study is to evaluate the effectiveness of our smartphone VR-PAT as a pain distraction tool during repeated at-home burn dressing changes among 100 children (age 6–17 years, inclusive) with a burn injury in comparison to 100 children with a burn injury who do not use the VR-PAT.

Three specific aims will be pursued by recruiting a total of 200 pediatric burn patients (6–17 years) from two large burn centers:Aim 1: Evaluate the effectiveness of VR-PAT for pain management and opioid pain medication reduction during at-home burn care.*Hypothesis 1*: VR-PAT will induce clinically meaningful pain score intensity and opioid consumption (PIOC) reduction (>30%) during at-home burn care.Aim 2: Examine continuous engagement of patients and caregivers with VR-PAT during repeated at-home burn dressing changes.*Hypothesis 2*: Pediatric patients remain effectively engaged and interested in using the VR-PAT during repeated at-home burn dressing changes.Aim 3: Determine if there is a pain threshold for VR effectiveness.*Hypothesis 3*: VR-PAT is less effective for patients who have minor pain (Numeric Rating Scale (NRS) 1–2) than compared to moderate or severe pain.

### Trial design {8}

We will conduct an RCT with a 1:1 allocation ratio to either the *intervention group* (VR-PAT headset group) or the *control group* (no VR headset or game was provided). Pain, anxiety, and VR engagement (for those in the intervention group) will be assessed daily with each home dressing change for about 1 week.

## Methods: participants, interventions, and outcomes

### Study setting {9}

Participants will be recruited from American Burn Association-verified burn centers in the Midwest (Nationwide Children’s Hospital (NCH), Columbus, Ohio) and Southwest (Parkland Health, Dallas, TX). The list of study sites can be obtained on ClinicalTrials.gov or by contacting the corresponding author. The institutional review board (IRB) at NCH approved the study protocol under a single IRB agreement with the University of Texas Southwestern Medical Center.

### Eligibility criteria {10}

Eligibility will be assessed using the following criteria: (a) undergoing treatment for acute burn injury; (b) age 6–17 years, inclusive; (c) receiving their first outpatient clinic dressing change or being discharged from the ED or inpatient burn unit; (d) having a dressing that requires daily changes at home for about 5 days after their first outpatient appointment or discharge from the hospital; (e) patient and family caregivers can communicate (read and write) using English or Spanish; and (f) report an NRS pain score of ≥ 1 (NRS 0–10 with 10 being worst pain) from the most recent dressing change. To minimize the possibility of confounding variables, the following exclusion criteria will be applied: (a) any wounds that may interfere with study procedures (i.e., face burns); (b) vision, hearing, or cognitive/motor impairments preventing valid administration of study measures; (c) history of motion sickness, seizure disorder, dizziness, or migraine headaches precipitated by visual auras; (d) minors in foster care, prisoners, or those who are currently pregnant; (e) suspected child abuse; (f) unable to communicate in English or Spanish; and (g) families who do not have access to a VR compatible smartphone.

### Who will take informed consent? {26a}

Once patients are screened as eligible to participate, research study coordinators will approach the legal guardian and eligible child in the hospital (if inpatient) or Outpatient Burn Clinic for consent. Coordinators will ensure that the assenting child is awake, alert, and willing to be approached for research. Research staff will proceed with consent if both the patient and the patient’s guardian are interested in participating in the research after the study introduction by the care team. During the consent, the coordinator thoroughly ensures that the participant and guardian understand the research study, their role in participation, that participation is voluntary, would not affect treatment, and that they can withdraw at any time. The participants and guardians are informed of any risks associated with participation, and that participation in the study does not have any additional costs to their standard of care treatment. Once all questions are answered, the legal guardians give written consent, and the pediatric patient over 9 years of age gives written assent (per IRB guidelines).

### Additional consent provisions for collection and use of participant data and biological specimens {26b}

During the caregiver and participant’s informed consent conversation, the caregiver will be asked for permission to store the subject’s protected health information (PHI) and identifiable information for future IRB-approved research. The caregiver (parent/guardian) can opt out of this option, which will not affect their standard of care treatment. Biological specimens will not be collected for this study.

## Interventions

### Explanation for the choice of comparators {6b}

VR-PAT is a standalone mHealth tool that was developed at NCH and thoroughly tested in this patient population [19, 20]. It does not require an internet or Wi-Fi connection beyond downloading the app and consists of a lightweight VR viewer and an engaging Virtual River Cruise game played on a smartphone. Children play the virtual game by slightly tilting their heads without arm or hand movement, minimizing interference with the dressing change. A standard of care comparator was chosen as this study is conducted at home. We want this distraction tool to fit into the home setting in the future, so comparing it to what families would be doing otherwise was a critical aspect.

### Intervention description {11a}

The Virtual River Cruise game within the VR-PAT system allows a child to gently cruise on a boat and aim for the snow-blowing statues along the banks of the river. The statues emit snow if the child correctly aims at them, and a thermometer placed in the front of the boat shows decreased temperatures as more snowflakes are blown. As feedback to reinforce continued engagement, a scoreboard placed beside the thermometer will show children the number of statues they have activated. Additionally, as the temperature drops, snow and ice will start piling up on the boat and its surroundings, providing an enhanced “cooling” experience for pediatric burn patients. The directionally adaptive audio matches the progress of the game and the direction in which a child’s head is turning, further enhancing the immersive experience of VR-PAT during burn dressing changes. The active VR game can last indefinitely, so it can be used for the entire at-home dressing change with a charged battery without being interrupted. VR-PAT will be delivered by whoever is helping the child in the intervention group with their dressing change. Each participant in this group will complete one session for each required dressing change for about 1 week.

### Criteria for discontinuing or modifying allocated interventions {11b}

VR intervention group participants will be advised to discontinue using the headset during a dressing change if it causes motion sickness, headaches, nausea, or dizziness. Participants are welcome to try using the headset again for the next change but have the option of continuing the dressing changes and surveys without it or withdrawing from the study. Any adverse events from participation will be noted and reported on the subject surveys.

### Strategies to improve adherence to interventions {11c}

To improve study completion and participation, all subjects will receive a VR headset and an app download for their participation in the study. After returning the daily surveys, participants will receive $25 on a Greenphire ClinCard. Study team coordinators will encourage completion and adherence to the protocol by offering various options for follow-up. Surveys can be returned in person, by mail via a pre-paid envelope, or scanned and emailed to the coordinator. The study team will conduct calls before the follow-up appointment and up to three calls after to remind subjects to return surveys.

### Relevant concomitant care permitted or prohibited during the trial {11d}

The use of concomitant medications is allowed per the standard of care for treating the burn injury and pain management. Caregivers are requested to note the medication and the dosage on the caregiver survey report for each day they are used.

### Provisions for post-trial care {30}

Not applicable. No post-trial care is provided to study participants. No compensation is provided to participants who are harmed by participation.

### Outcomes {12}

#### Primary outcome measure

Change in self-reported and caregiver-reported worst pain, average pain, and time spent thinking about pain (NRS 0 (min)–10 (max)). These pain questions are assessed at each dressing change for about 1 week. Changes in pain will be compared between the intervention and control groups.

#### Secondary outcome measures

Change in self-reported anxiety (Spielberger State-Trait Anxiety Inventory for Children (STAI-CH) score 6 (low anxiety)–24 (high anxiety)). Anxiety is assessed at baseline (recruitment visit) and before each dressing change for about 1 week. The changes in anxiety will also be compared between the intervention and control groups.

Pain medication reduction. The caregiver will report pain medication usage (name and dosage) for about 1 week after each dressing change. The pain medication used will be compared between the intervention and control groups.

Average self-reported VR experience (NRS 0 (min)–10 (max) for the degree of realism, pleasure, and satisfaction with VR). For about 1 week, these VR experience questions are assessed at each dressing change for those in the intervention group.

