### Sample size {14}

The sample size was calculated for the primary outcome of the child-reported overall pain score. We consider a 30% reduction in the pain NRS score as a minimal clinically meaningful reduction in pain. According to our previous publication on pain reduction of VR-PAT among pediatric patients 6–17 years of age who were treated at our outpatient burn clinic [19], the pooled standard deviation (SD) of the child-reported overall pain visual analog scale (VAS) score was estimated. Aiming at detecting a 30% reduction of the pain score in the VR-PAT group compared with the control group at any of the first 7 days of follow-up, and assuming the same SD on these days, we will need 89 subjects per group to achieve 80% power and a two-sided type-I error of 0.01 at each day using a two-sample *t*-test. The type-I error rate is adjusted by Bonferroni correction for multiple comparisons. Assuming a 10% dropout rate, we will need 99 subjects per group. Based on this calculation, we plan to *n* = 100 subjects per group (*n* = 200 subjects total).

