### Recruitment {15}

Participants will be recruited after their first dressing change in the Outpatient Burn Clinic or at discharge from the ED or inpatient burn unit. Patients of age will be initially screened daily through the electronic medical record system at each hospital for general eligibility. Once the treating clinician assesses the burn wound and determines the type of dressing needed, trained research staff will approach patients receiving a daily dressing to assess their pain status and smartphone availability. Study introductions are made during this in-person visit, and informed consent/assent is obtained from interested caregivers and patients. No recruitment materials will be used to advertise the study.

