### Concealment mechanism {16b}

Study participants are randomized into control and intervention groups after signing consent and completing the baseline survey. Research recruiters and subjects do not know the intervention assignment until the subject is randomized in REDCap.

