#### Child surveys (self-reported)

All participants (control and intervention group) will self-report anxiety prior to the dressing change using the STAI-CH scale with ratings from not at all to very much. After the dressing change is completed, the child will answer the remaining survey questions assessing overall pain score (NRS, 0–10), worst pain score (NRS, 0–10), and time spent thinking about pain (NRS, 0–10). The survey is completed once daily alongside dressing changes for 7 days until the patient returns for their follow-up appointment. Survey questions remain the same for each daily dressing change.

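### The anxiety outcome is a change from a recruitment-visit baseline that is not like-for-like with the pre-dressing home scores; adjusting for that baseline would be clearer and more precise than subtracting it

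*Protocol article*

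**What the plan says.** Under Outcomes {12}, Secondary outcome measures, the protocol article lists change in the child's STAI-CH score (range 6 to 24) and gives its timing: "Anxiety is assessed at baseline (recruitment visit) and before each dressing change for about 1 week". It continues: "The changes in anxiety will also be compared between the intervention and control groups".

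The situation in which each score is taken has to be put together from other sections:

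- **Recruitment {15}** fixes the point of entry: "Participants will be recruited after their first dressing change in the Outpatient Burn Clinic or at discharge from the ED or inpatient burn unit".
- **Eligibility criteria {10}:** a child qualifies on a pain score "from the most recent dressing change", so at least one change has already taken place at entry.
- **Concealment mechanism {16b}** gives the order of events: "Study participants are randomized into control and intervention groups after signing consent and completing the baseline survey".
- **Child surveys (self-reported):** children in both arms "will self-report anxiety prior to the dressing change using the STAI-CH scale".

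Statistical methods {20a} names no analysis for STAI-CH. Adjustment for the baseline score is therefore neither stated nor ruled out.

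**The concern.** The reference score comes from a visit that follows a clinic dressing change or falls at discharge from the ED or ward. Each later score is anticipatory, because it is taken just before a home change. Anxiety of this kind depends on the moment at which it is reported. Subtracting one score from the other therefore combines any real movement in procedural anxiety with the difference between the two situations. That difference may also vary between children, because they enter by three routes.

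Two things are at stake:

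- **Interpretation.** Scores could appear to rise from baseline in both arms simply because of when the baseline was taken. A reader shown such changes could take them for worsening, or for a response to treatment.
- **Precision.** The baseline is already collected, and subtracting it is not the most efficient way to use it.

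**Working it through.** **Plan figure to reproduce.** There is none for anxiety: the article gives no SD, effect size, power or correlation for STAI-CH. The trial is sized on child-reported pain: "we will need 89 subjects per group to achieve 80% power and a two-sided type-I error of 0.01 at each day" and "Assuming a 10% dropout rate, we will need 99 subjects per group". The dropout step checks, since 89/0.9 = 98.9, which rounds up to 99. The 89 is used below only as a realistic evaluable group size.

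**Timing, side by side.**

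| Score | When taken | Relation to a dressing change |
|---|---|---|
| Baseline | Recruitment visit, before randomisation | After a clinic change, or at discharge |
| Home scores | Each home change, about 1 week | Just before the change |

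The two are not like-for-like within a child. The timing rule is the same in both arms and is applied before allocation is known.

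**Bias.** A situational shift common to both arms cancels in the between-group difference. A simulation confirms this (4,000 replicates, 89 per group, r = 0.3, a common 2 SD shift from baseline to home, true effect −0.50 SD):

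| Estimator | Mean estimate | Empirical SE |
|---|---|---|
| Change score | −0.498 | 0.180 |
| Home score alone | −0.498 | 0.150 |
| Home score adjusted for baseline | −0.498 | 0.145 |

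All three are unbiased to simulation accuracy. They differ in precision.

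**Precision.** Let s be the common SD of the baseline and home scores and r their correlation, at one time point. The per-child variances that drive the contrast are:

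- home score alone: s²
- change score: 2s²(1 − r)
- home score adjusted for baseline (ANCOVA): s²(1 − r²)

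Change minus ANCOVA is s²[2(1 − r) − (1 − r²)] = s²(1 − r)², which is positive for every r below 1. The ratio is 2(1 − r)/(1 − r²) = 2/(1 + r).

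| r | Change | Home alone | ANCOVA | Change ÷ ANCOVA |
|---|---|---|---|---|
| 0.2 | 1.60 | 1.00 | 0.96 | 1.67 |
| 0.3 | 1.40 | 1.00 | 0.91 | 1.54 |
| 0.5 | 1.00 | 1.00 | 0.75 | 1.33 |
| 0.7 | 0.60 | 1.00 | 0.51 | 1.18 |

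Change is worse than the home score alone only when 2(1 − r) > 1, that is r < 0.5. With unequal SDs the threshold becomes r < SD(baseline)/(2 × SD(home)).

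**What this means in children.** The following are assumptions, not taken from the article: effect 0.5 SD, two-sided alpha 0.05, equal SDs, one time point. The number per group for 80% power is 2v(1.960 + 0.842)²/0.5² ≈ 62.8v, rounded up, where v is the variance factor above. Power is at 89 per group.

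| r | n per group: change / home alone / ANCOVA | Power: change / home alone / ANCOVA |
|---|---|---|
| 0.2 | 101 / 63 / 61 | 75.1% / 91.6% / 92.6% |
| 0.5 | 63 / 63 / 48 | 91.6% / 91.6% / 97.1% |
| 0.7 | 38 / 63 / 33 | 99.1% / 91.6% / 99.7% |

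**The case against.** The strongest reply is that the article never defines the outcome as home score minus baseline and uses the word change loosely. Its pain outcome is also called a change, yet no baseline pain score is listed there, and Aim 1 analyses the raw daily scores. The Abstract speaks of a difference between groups over the week. Since no anxiety model is given, the choice between subtracting, adjusting and ignoring baseline could be left to the analysis plan.

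Part of this stands: subtraction is the natural reading, not a stated formula. For anxiety, though, the article puts a named baseline directly beside the word change and compares the changes. The definition of an outcome belongs in the protocol. If raw home scores are meant, the wording still needs correcting.

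Other replies also have force:

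- The loss against ANCOVA applies to any simple change score, even one with a perfectly matched baseline. The 1.18 to 1.67 range is therefore not a measure of the timing mismatch.
- A mismatch makes a low r plausible, but nothing in the article shows that r is low. At r = 0.7 the change score beats the home score alone, with 38 against 63 per group.
- The article does not say whether the baseline items refer to the present moment or to the last dressing change. Nor does it say that children at discharge have no change ahead of them; all of them face daily home changes.
- Only a between-group comparison is planned, and the outcome is secondary.

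**Conclusion.** The point holds as one of interpretation and efficiency, at low severity. The within-child change is not a like-for-like measure of procedural anxiety. If change is home score minus baseline, an unadjusted comparison of changes is less precise than covariate adjustment at every r below 1. With equal SDs the variance is 1.67 times as large at r = 0.2, 1.33 times at 0.5 and 1.18 times at 0.7.

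A reader might infer either of two stronger claims, and the article supports neither:

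- **That the treatment comparison is biased.** It is not, because the baseline precedes randomisation and is timed alike in both arms.
- **That subtracting baseline is worse than ignoring it.** With equal SDs that requires r below 0.5, and no r is given.

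The variance figures rest on equal SDs and a single time point. The sample sizes and power rest in addition on the assumed 0.5 SD effect and 5% alpha.

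**What to change.** In Secondary outcome measures, define the anxiety outcome as the pre-dressing home STAI-CH score (6 to 24), compared between groups with the pre-randomisation STAI-CH score as a covariate. State that within-arm change from the recruitment visit will not be interpreted as treatment response. It would also help to say at what moment in the visit the baseline scale is completed and what period its items refer to. Recruitment route (clinic, ED or inpatient discharge) may be added as a covariate only if it is already recorded; the article does not say that it is.

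The cost is a small change to the wording of one secondary endpoint. No extra assessment of children is needed, because the baseline score is already collected before randomisation.
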